### Overview of the intervention package

The interventions will be developed through a consultative process, requiring stakeholders to reflect on how their programs can bring change. The following broad interventions will be developed and tested:

Strengthening the health care system and surveillance system for early reporting of suspected cases of human and animal anthrax by developing and implementing the “One-Health” bio-surveillance system.Establishment of an anthrax diagnosis facility in the state to facilitate early diagnosis and reporting of anthrax cases based on standardized case definitions.Operationalization of standard operating procedures and outbreak response protocols for all stakeholder departments in a consultative manner.Provision of postexposure prophylaxis of suspected contacts by the health department at the health facility and community.Livestock vaccination program by the state on a large scale and strategy of “ring vaccination” during outbreaks followed by a cost-benefit analysis of the same.Placing a framework for categorization of geographical “Risk-Zones” based on GIS mapping of cases for prioritization of public health interventions.Capacity building of stakeholders for early detection and appropriate action at district, sub-district, block, and village level, including clinical case management and referral.Targeted and generalized IEC/BCC activities to be implemented round-the-year by the state departments in a coordinated manner.

### Study procedures

We will use a team approach, with external and domain expert representation for the development and effective implementation of our intervention model. Please see [Table 2] for the schedule of enrollment, intervention, and assessment. The details of the teams and their compositions, responsibilities, and activities are provided in [S1 Appendix]. The interventions would be implemented in the entire district in partnership with various departments of the state (Health, Animal resources, Forest, and Environment & local governance) in the following manner:

Developing a “Risk zoning” protocol based on surveillance data available on the previous number of cases (both human and animal) from different units in the district. Geographic Information systems mapping will be done on a real-time basis to categorize the geographical limits of the district into a RED (Action), YELLOW (Alert), and GREEN (Monitor) zones during and following an outbreak. Capacity building, surveillance, and IEC/BCC activities shall depend on the prioritization zone of the location.Advocacy for a strong free-of-cost routine and outbreak (ring) vaccination program in the district using findings of the cost-benefit analysis, desk review, and baseline study.Development of departmental and interdepartmental Standard Operating Procedures for both exclusive and inter-operable activities and conduct of multi-departmental coordination meetings.Development of training and capacity building materials for each stakeholder group, finalization of training calendar, and micro plan followed by conduction of Training for capacity building among Primary Stakeholders from different departments (Health, Veterinary, Forest & Environment, local governance bodies). Training on case definition, early diagnosis, reporting cases, sample collection will be done at the district level.Development of IEC material for each group of stakeholders and assisting the state in carrying out IEC and BCC activities in the community. BCC strategy will be developed using Social Cognitive Theory, which depicts that behavior change in humans can be explained by a triadic interaction of behavior, personal and environmental factors [22].Strengthening of surveillance for anthrax by developing surveillance protocols by adaptation of WHO protocols, testing, and implementing the surveillance system, and facilitating a regional diagnostics service for anthrax as per the case definitions and diagnostics protocol provided in [S2 Appendix].

**Table 2 pone.0251041.t002:** Schedule of enrollment, intervention, and assessments.

	Year 1		Year 2		Year 3	
TIMEPOINT**	Q. 1 &2	Q. 3 & 4	Q. 1 &2	Q. 3 & 4	Q. 1 &2	Q. 3 & 4
ENROLLMENT:						
• *Eligibility Screen*	X					
• *Informed Consent*	X					
• *Baseline Survey*	X					
INTERVENTIONS:						
• *Interventions Implementations*		X	X	X		
ASSESSMENTS:						
• *End line Survey [baseline variables*: *see* Table 3*]*					X	
• *Qualitative assessment of the effectiveness of public health interventions*						X

### Multilevel multi-departmental coordination

Multi-departmental coordination is an essential component for effective implementation of our intervention model and therefore we have developed the multi-departmental coordination teams at multi-levels which will ensure the departmental and multi-departmental coordination of planned activities. The figure given below may give you an overall picture to understand the actual coordination at different levels among different departments [Fig 2].

**Fig 2 pone.0251041.g002:**
[figure not shown]
Stakeholders for multilevel multi-departmental coordination.

### Study timeline

#### Participant selection

A list of total Gram Panchayats and total number of villages will be made for all the fourteen blocks. From each block two Gram Panchayats, and four villages from each Gram Panchayat will be selected based on simple random sampling using random number generation method. In this way, 2640 individuals from 112 villages will be selected for quantitative data collection during baseline and end line. Systematic random sampling will be used to select the households for the survey in the selected villages. Beginning of the survey will be from the middle point of the village and only one individual will be enrolled as participant from each house. The randomization process from district to household level at each step will ensure that the sample size selected for our study will be representative for the larger population of Koraput.

Quantitative data will be collected regarding the knowledge of the anthrax disease, attitudes towards curbing it, and practices among villagers that led to the rise of cases as given in Table 3. Data will be collected using electronic data capture tools. Enrolment of participant has started from 16^th^ June 2020 and will be finished by the month of October 2020. End-line study will take place as per the schedule mentioned in the study timeline [see Table 2]

**Table 3 pone.0251041.t003:** Content of the baseline survey.

Topics and Constructs	Description
Socio-economic and demographic characteristics	Gender, age, residency, education, religion, caste, household members, occupation, family income etc.
Information on domestic animals	Existence of livestock, number of livestock, types, the purpose of keeping livestock, place of keeping livestock, involvement with livestock, the place for grazing, frequency of taking for grazing, the experience of animal handling, dispose of solid and animal waste products
Vaccination	Awareness about animal vaccination, the practice of vaccination, type of animals vaccinated, attitude towards animal vaccination, frequency of vaccination, reasons for not getting animals vaccinated, place of vaccination, the cost for vaccination
Practices of animal handling	Practices of dead animals’ burial, symptoms observations during deaths, information on recent animal death, de skinning practices with dead animals, use of protective equipment for skinning, govt. financial support for burial and death compensation
Food habits	Consumption of meat, type of meat they consume, sources of getting meat, ways of consuming, frequency, preservation of meat, consumption of animal blood
Knowledge and awareness about anthrax	General awareness, source of information, Local names, transmission, behavior/practices with suspected and dead animals due to anthrax, reporting structure, ways of treatment, information of cases in recent past, activities are done for awareness, knowledge about human anthrax, symptoms in humans, experience with human anthrax

Focus group discussions (FGDs) from 4 blocks (2 endemics and 2 nonendemic) blocks of the district will be carried out to provide insight into the process of intervention delivery, how it affects behavior and practices changes, and how this model is perceived and valued. Key person interviews and in-depth interviews will be carried out to assess the feasibility and identify the bottlenecks in the implementation processes from the systems side as well.

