### Study participants

Participants will be enrolled by following the inclusion and exclusion criteria given below:–

Inclusion criteria: Participants will be selected based on the eligibility criteria: a) Should be an adult (age above 18 years) and a permanent resident of Koraput district, b) willing to participate in the study.Exclusion criteria: a) Cognitive impairment, b) having onset symptoms or infected with any of the communicable disease which can be spread through nasal or mouth droplets.

The study participants for the baseline and end-line study will be sampled from the stakeholders identified in the district. A comprehensive stakeholder mapping and analysis will be carried out based on the broad categories outlined in [Table 1].

**Table 1 pone.0251041.t001:** Identified groups of stakeholders to be included in the study.

Health Care Sector	Animal Care Sector	Community
**Clinical service providers**	Veterinary doctors	Service utilizer clients
**Program managers**	Livestock inspectors	Local governance members
**Health workers**	Forest guards	Non-governmental organizations and Self-help groups
**Accredited social health activists (ASHAs)**		Cattle owners/grazers
		Hunter/gatherers
		Village residents

Additionally, participants for the qualitative study will be selected purposively from the known hotspots of outbreaks and tribal communities with practices that make them vulnerable for anthrax infection, acquisition, and propagation.

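### The household stage starts at a fixed central point and takes one adult per house, so as written it does not support the claim that randomisation at each step ensures a representative sample

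*Protocol article*

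**What the plan says.** All of this is in the protocol article, mainly under Participant selection.

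- Upper stages: two gram panchayats are drawn per block, and "four villages from each Gram Panchayat will be selected based on simple random sampling using random number generation method".
- Households: "Systematic random sampling will be used to select the households for the survey in the selected villages". The next sentence sets the start: "Beginning of the survey will be from the middle point of the village".
- Person: "only one individual will be enrolled as participant from each house". Study participants defines who may be taken: "Should be an adult (age above 18 years) and a permanent resident of Koraput district", if willing.
- Size: "2640 individuals from 112 villages will be selected for quantitative data collection during baseline and end line".
- Assurance: "The randomization process from district to household level at each step will ensure that the sample size selected for our study will be representative" of the wider population of Koraput.

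The article gives no random first house, direction, sampling interval or household list, and no rule for choosing among the adults of a house.

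**The concern.** A systematic sample gets its randomness from its start. With a fixed start, route and interval, each house is either certain to be chosen or cannot be chosen. Gram panchayats and villages are drawn by random number, but the only start rule stated for households is a fixed place. The article nevertheless counts this stage among its randomised steps and rests a guarantee of representativeness on it.

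Taking one adult per house adds a second departure. Even if that adult is picked at random, a person living with three other adults has a quarter of the chance of a person living alone. Unweighted estimates therefore lean towards small households.

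Two results are exposed. One is the survey prevalence, for which the sample was sized. The other is the survey comparison of baseline with end-line. The study is single-arm (Study design) and Data analysis makes that comparison the primary one, so no concurrent group would show that a change came from a different mix of respondents.

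**Working it through.** **1. The plan's own figure.** Sample size determination gives Z = 1.96, P = 5%, d = 20% of P = 0.01, design effect 1.3 and non-response 10%.

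- 1.96² × 0.05 × 0.95 / 0.01² = 1824.8
- × 1.3 = 2372.2
- × 1.1 = 2609.4, against the stated 2608 (dividing by 0.9 instead gives 2635.8)

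The figure reproduces closely. It does not decide this point, but it gives the yardstick: a planned margin of ±1.0 percentage point around 5%.

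**2. What the stated household stage provides.** The stated method needs a random start. The stated start is the village centre. The interval may be wide or narrow. A wide one helps coverage, but it does not make a fixed start random.

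**3. Coverage of the village.** Interviews per village: 2640 / 112 = 23.6. Mean village: 1.37 million / 2028 = 676 residents (Study setting). At an assumed 4 to 5 persons per household, that is 169 to 135 houses. If a team works outward from the centre and stops after 23.6 interviews (also an assumption), the share of the village reached is interval × 23.6 / houses:

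| Interval | 169 houses | 135 houses |
|---|---|---|
| 1 (every house) | 14% | 17% |
| 3 | 42% | 52% |
| 6 | 84% | 100% |
| 7 | 98% | 100% |

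The interval that just spans the village is houses / interviews, or 5.7 to 7.2. Below it the outer houses are missed; at or above it they are not. The article does not say which applies.

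**4. A change in who answers.** Assume exposure of 8% in men and 2% in women. With a share m of men, the survey estimates 2% + 6% × m.

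- m = 0.50: 5.0%
- m = 0.35: 0.35 × 8% + 0.65 × 2% = 4.1%

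That is a fall of 0.9 points, or 0.9 / 5.0 = 18% relative, with no true change. Smaller shifts give proportionately less: 5 points fewer men gives 0.3 points (6%), and 10 points fewer gives 0.6 points (12%). With a weaker assumed contrast of 6% against 4%, the 15-point shift gives 2% × 0.15 = 0.3 points (6%). Standardising both rounds to half men and half women gives 5.0% each time, and the spurious change disappears.

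**5. Cost of household-size weights.** For equal-chance households the variance factor is E(k²) / [E(k)]², where k is the number of adults. Two assumed distributions:

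- 15%, 45%, 20%, 15% and 5% of houses with 1 to 5 adults: 7.4 / 2.5² = 1.18
- 10%, 60%, 20% and 10% with 1 to 4 adults: 5.9 / 2.3² = 1.12

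Intervals widen by the square root, about 6% to 9%.

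**The case against.** The strongest reply is that the article does name systematic random sampling, and that a central start is compatible with a random direction or with an interval covering the whole village. This stands in part. It rules out saying that the household stage is shown to be non-random. It does not rescue the guarantee, because the only start rule given is a fixed one.

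The article's randomisation sentence also stops at the household. The unstated choice of adult therefore does not contradict it and bears only on representativeness. How the adult is picked, when visits take place and whether there are call-backs are field details that a condensed article may leave to the full protocol. Their absence is not held against the plan here.

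A reader might infer that outlying hamlets are left out, that whoever is at home is over-represented, and that high-risk exposure is therefore under-sampled. The document does not support this. It states no stopping quota, interval or visiting hours. Study participants says both surveys will sample from the identified stakeholders, and Table 1 lists grazers and hunter/gatherers among them.

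A bias that is the same in both rounds would partly cancel in the comparison, though not in the prevalence. The article also leaves open whether end-line re-interviews the same people. If it does, the mix could shift only through losses. Finally, human cases and deaths come from the surveillance programme, and animal cases and vaccination coverage from the veterinary department (Data analysis), so household selection does not touch them.

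**Conclusion.** The point holds in a limited form. The stated household stage, with its fixed central start, no stated random element and one adult per house, does not support the assurance that randomisation at each step secures a representative sample. Unequal selection chances by household size follow directly from the one-adult rule. Incomplete coverage is conditional: it arises only if the interval is shorter than about 6 to 7, on the assumed household size and outward working.

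The 18% apparent fall illustrates how exposed a single-arm before-after comparison is to a changed mix of respondents. It rests on assumed exposure rates and an assumed 15-point shift in sex mix, and is not a forecast. At 0.9 points it is close to the whole planned margin of 1.0 point; milder assumptions bring it down to 0.3 points. The consequence is confined to the survey results.

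**What to change.** 1. **Analysis of both rounds.** Weight for household size and standardise baseline and end-line to one age-by-sex distribution, either the pooled sample or the district's adults. Report this beside the crude comparison. Table 3 already lists age, gender and household members. The exact weight is the number of eligible adults, so end-line should record that number if the household item does not separate adults. The cost is analysis time and slightly wider intervals. This does not correct selection of central over outlying houses. The pooled sample needs no outside figures; the district distribution is not in the article and would have to be obtained.
2. **Wording.** Replace the guarantee of representativeness with a plain description: gram panchayats and villages were drawn at random, and households were sampled systematically from a fixed central start. If a random direction or first house was in fact used, say so and give the interval. This costs nothing.
3. **Fieldwork, only where comparability allows.** Use a random starting house with interval = households / interviews, run across the whole village including its hamlets. Baseline enrolment began in June 2020 and was due to finish by October 2020, so many villages may already have been done from the centre. For those, keep the same rule at end-line or report the difference, because a changed rule could itself produce an apparent change. Call-backs are optional.

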### Data analysis

Effectiveness of our complex public health intervention package will be analyzed as a whole One Health strategy instead of its separate components for elimination of human anthrax cases in endemic regions. Furthermore, the impact of each intervention will be tracked through the logic model developed by us with different levels such as inputs, activities, outputs, indicators, outcomes & impact [Table 4 in S3 Appendix]. Our quantitative and qualitative surveys during baseline and end line will be analyzed to observe the effectiveness of implementation of our intervention package and to observe the improvement in knowledge, behavior, and practices with regards to the anthrax disease among communities residing in the Koraput district. Annual data of animal vaccination, animal and human anthrax cases and deaths will also be an analysis to see the progress and track the effective implementation of our intervention package. The data of human anthrax cases and deaths will be taken from IDSP (Integrated Diseases Surveillance Program) Odisha and similarly the data of animal vaccination coverage, animal anthrax cases and deaths will be taken from Veterinary department in the district. At the end of the 3 years, we will do a comparative analysis of vaccination coverage, animal and human anthrax cases and deaths in the district to find the effectiveness of our interventions. Descriptive statistics will be used for the analysis of quantitative data though SPSS (Statistical Package for Social Sciences) or STATA. Qualitative data will be analyzed through thematic analysis, and network diagrams. The primary comparison of baseline and end-line data will be made by applying tests of statistical significance where applicable, with a level of significance established at p = 0.05. Moreover, bottleneck analysis will be done using appropriate models for the surveillance system in place and finding of this study will be published in open access journal upon completion of study [23].

## Discussion

The study is for three years based on implementation models including surveys (baseline and end line), capacity building, and sensitization of various stakeholders from the department of health, veterinary, and forest systems at various levels in a tribal district of Odisha, India. The prevalence and outbreaks of anthrax are interlinked with the animal-environment-human context, which signifies the need for collaborative, transdisciplinary, and multi-sectoral approaches for the prevention and control of anthrax [24]. The intervention builds upon a preliminary study to strengthen the health care and surveillance system for early reporting of suspected cases of human and animal anthrax by developing and implementing the “One-Health” strategy. We aim to eliminate incidences of human anthrax cases to zero by the end of three years using a multi-sectoral team-based approach. We also propose for sustainable on-ground investigation and surveillance after this intervention-implementation in collaboration with health, veterinary, forest and other allied departments in the district and state. Effectiveness of the capacity building training for enhancing knowledge will be assessed by structured pre- and post-assessments. Findings from this study would provide recommendations for policymaking and future scale-up planning to the elimination of zoonotic diseases using ‘One Health’ strategies. Moreover, the study protocol may further be replicated in other endemic regions of India as well as other countries.

## Abbreviations

ANM: Auxiliary Nurse Midwife
ASHA: Accredited Social Health Activist
BCC: Behaviour Change Communication
CBT: Capacity Building Training
CDMO: Chief District Medical Officer
CDVO: Chief District Veterinary Officers
CHC: Community Health Centre
CTRI: Clinical Trial Registry- India
FHW: Female Health Worker
GIS: Geographic Information System
IDSP: Integrated Disease Surveillance Programme
IEC: Information Education Communication
MDC: Multi Departmental Coordination
MHW: Male Health Worker
MO: Medical Officer
MPH: Master of Public Health
NCDC: National Centre for Disease Control
NIVEDI: National Institute Of Veterinary Epidemiology And Disease Informatics
PCR: Polymerase Chain Reaction
PHC: Public Health Centre
RMRC: Regional Medical Research Centre
SC: Sub-Centre
ToC: Theory of Change
